**2.2. Study variables**

The study variables are the socio-demographic characteristics and factors related to acceptability indicators why they accept, how they want it to be, who should deliver the service and others.

**2.3. Data collection techniques and tools**

Data collectors will find the names of ex tuberculosis patients from tuberculosis unit registers and list them out according to the study clusters. Based on the number and sample size they will randomly select ex tuberculosis patients from all intervention cluster to participate in the study.

During data collection if they found that the ex tuberculosis patient has died or moved to other community they will replace her/him by next ex tuberculosis patient on the list. If they come across ex tuberculosis patient less than 18 years old, they will interview head or guardian of the household.

In addition to find out the acceptability by the community, data collectors will interview household next to ex tuberculosis patients household if they know about tuberculosis treatment. If they do not know will proceed on the next right side household and interview guardian head of the household.

A standardized pretested questionnaire including socio-demographic variables and factors affecting acceptability will be included in the questionnaire. Programme coordinators and the investigator will give training to health workers about administering the questionnaire. Trained data collectors will administer the interview preferably by those who can speak the local language.

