**Study - IV**

This is a cross-sectional study to find the acceptability of community based tuberculosis care by health workers, community members, and tuberculosis patients. Health workers, tuberculosis patients and community members will participate in the study districts. The data collectors will randomly select tuberculosis patients, health workers, health extension workers, tuberculosis treatment supervisors and community health agents who are directly involved in tuberculosis patient care. From the community previously treated tuberculosis patients and community members living closer to tuberculosis patients, next fifth household heads will be taken. Trained data collectors will administer a pretested questionnaire about the acceptability of community-based TB care.

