**2. Methods**

**2.1. Study design**

This is a cross-sectional study to find out the acceptability of community based tuberculosis care. The study will include all health workers (health professionals, health extension workers and community health agents), community members, and tuberculosis patients who completed their treatment (ex tuberculosis patients) in the study sites. Based on the sample size, study subjects will be randomly selected from all intervention clusters. Community members next to treated tuberculosis patients will be included in the study. Next fifth household on the right side of treated tuberculosis patients’ house will be included. Health workers working in tuberculosis clinic, health extension workers and tuberculosis treatment supervisors will be included in the study.

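### Study IV gives two incompatible rules for choosing neighbour households, and one of them favours households that already know about TB treatment

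*Protocol*

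**What the plan says.** Three places in the protocol describe how community members are chosen for Study IV.

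- Section 6.2, Study IV, refers to "community members living closer to tuberculosis patients, next fifth household heads will be taken". No knowledge condition is attached.
- Study Four, section 2.1, says that neighbours of treated patients are included and then specifies "Next fifth household on the right side of treated tuberculosis patients". Again there is no knowledge condition.
- Study Four, section 2.3, introduces the neighbour interviews with the purpose "In addition to find out the acceptability by the community". It then says that "data collectors will interview household next to ex tuberculosis patients household if they know about tuberculosis treatment", and continues: "If they do not know will proceed on the next right side household and interview guardian head of the household".

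The protocol does not define what counts as knowing about tuberculosis treatment. It does not say whether the knowledge question is asked again at the replacement house, or whether households passed over are to be recorded.

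**The concern.** The same respondent group is selected in two ways. One rule uses a fixed interval and takes whoever lives there. The other starts at the adjacent house and makes the interview depend on prior knowledge. Section 2.3 is the section a data collector would be expected to work from, yet the two design descriptions say something else.

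Two things are at stake. First, field teams could each follow the protocol and still sample different households, so results pooled across clusters would mix two selection schemes. Second, a knowledge screen changes whose opinion is measured. The stated purpose is acceptability by the community, but the screened sample leans towards neighbours already familiar with the treatment. Because the term is undefined, each collector decides who qualifies.

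**Working it through.** **The plan's own figure.** Study Four, section 2.4, gives n = 351 from an expected acceptance of 64.5%, z = 1.96 and a margin of 5%. The printed formula is not legible in the text available, but the usual single-proportion formula reproduces the figure: n = z²pq/d² = 1.96² × 0.645 × 0.355 / 0.05² = 351.85, truncated to 351. The sample size does not depend on the neighbour rule, and this point does not alter it.

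**The rules side by side.**

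| Element | 6.2, Study IV | Study Four, 2.1 | Study Four, 2.3 |
| --- | --- | --- | --- |
| Household | fifth | fifth, on the right | adjacent, else next on the right |
| Knowledge condition | none | none | yes, undefined |
| Replacement | none stated | none stated | yes, for a household that does not know |
| Respondent | household head | not stated | head or guardian |

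**Do the rules pick the same house?** Number the houses to the right 1, 2, 3 and so on. Let k be the share of households that know about treatment, independent from house to house. The documents do not give k.

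- Fifth-household rule: always house 5.
- Section 2.3, single check (one skip, then interview whoever is there): house 1 or house 2, so never house 5.
- Section 2.3, repeated check: house 5 is chosen only if houses 1 to 4 do not know and house 5 does, with probability k(1 − k)⁴. At k = 0.5 this is 0.5 × 0.0625 = 3.1%. The largest possible value, at k = 0.2, is 0.2 × 0.4096 = 8.2%.

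So the rules almost never select the same household. Distance alone matters only if acceptance varies over a few doors, which the documents do not address.

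**What the knowledge screen does.** Let a₁ be acceptance among households that know and a₀ acceptance among those that do not. Acceptance among all neighbours is k·a₁ + (1 − k)·a₀.

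- Repeated check: the sample estimates a₁, so bias = (1 − k)(a₁ − a₀).
- Single check: the share of knowing households in the sample rises from k to k + (1 − k)k, so bias = k(1 − k)(a₁ − a₀).

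**Illustration.** These inputs are assumptions, not figures from the protocol.

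| Share not knowing | Gap a₁ − a₀ | Repeated check | Single check |
| --- | --- | --- | --- |
| 30% | 10 points | 3.0 | 2.1 |
| 30% | 25 points | 7.5 | 5.25 |
| 50% | 10 points | 5.0 | 2.5 |
| 50% | 25 points | 12.5 | 6.25 |

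If a₁ = a₀, the bias is zero on both readings. If those who know accept less often, the sign reverses: with a gap of −20 points and 50% not knowing, it is −10 points (repeated check) or −5 points (single check).

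**The case against.** The interval conflict is hard to dispute. One could read the adjacent household in section 2.3 as loose shorthand for the fifth household, since section 2.1 also speaks of neighbours next to treated patients before naming the fifth. Even so, the knowledge condition and the replacement step would still appear in one section only.

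The case against the rest is stronger, and much of it stands.

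- **Direction.** A reader might infer that the screen inflates acceptance. Study IV samples intervention clusters, where health workers hold monthly teaching sessions, so knowledge may partly mark contact with the programme. That makes upward bias plausible, but nothing in the protocol shows that those who know accept more often.
- **Strictness.** A reader might infer that collectors walk on until they find a household that knows. The text is "If they do not know will proceed on the next right side household" followed by an instruction to interview, with no repeated check stated. Both readings are open.
- **Yardstick.** It is tempting to set the illustrative bias against the 5-point margin in section 2.4. There, however, the proportion is defined for tuberculosis patients. No precision is stated for community members.
- **Lost households.** A reader might infer that skipped households go uncounted and that the extent of the screen can never be recovered. The protocol is silent on logging, and annex pages are missing from the text available, so a community-member form could not be checked.
- **Proximity.** Sampling near former patients is the design in all three places. Section 2.3 did not introduce it, and the fifth-household rule shares it.
- **The screen itself.** Asking only people who know a service whether they accept it is a defensible choice. It then needs to be stated as the target, and sections 6.2 and 2.1 do not do so.

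**Conclusion.** The point holds as a contradiction in the selection rule. Sections 6.2 and 2.1 take the fifth household unconditionally. Section 2.3 takes the adjacent household if it knows about treatment, and otherwise the next on the right, with the repeat of the check left unclear. The two rules select different households in nearly every case, and on either reading section 2.3 over-represents households that know.

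The estimate would then not represent community members near former patients if acceptance differs by knowledge. That condition is unverified. The documents support no direction or size, and the 2.1 to 12.5 point range rests wholly on the assumed inputs above. The protocol does not support a claim that community acceptability is overstated by a known amount.

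The reach is limited to one respondent group in a descriptive cross-sectional sub-study. The randomised treatment-outcome comparison in Study II is unaffected. Correction is still worthwhile, because the protocol itself fixes the rule in two ways and the remedy is cheap.

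**What to change.** State one household rule in section 6.2 and in Study Four sections 2.1 and 2.3, for example the fifth household on the right. Remove knowledge of treatment as a condition for interview. Give every respondent the same brief description of community-based treatment, record knowledge of TB treatment as a questionnaire item, and report acceptability overall and by knowledge.

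If the investigator prefers to keep the knowledge condition, define what counts as knowing and say whether the check is repeated at the replacement house. Name the target population as informed neighbours, and log and report the households skipped.

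The cost is protocol wording, one extra question and slightly longer interviews. The main drawback of the first option is that respondents new to the service answer on the strength of a short description, which is not the same as an opinion formed from experience. Reporting by knowledge lets the reader see how far that matters.

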**2.4. Sample size calculation**

In a study conducted in the Tigray, northern part of Ethiopia, it showed that 64.5 % community health workers accepted community based tuberculosis care. [38]

n =

Where: n = the sample size

p = the proportion of tuberculosis patients who accepted community-based tuberculosis care

q = 1- p z = the percentage level at 95% confidence interval (1.96)

d = the margin of error = 5% Based on this

n = = 351

**STUDY FIVE - TO FIND OUT THE PROPORTION OF TUBERCULOSIS PATIENTS INFECTED WITH HIV**

**1. Objective**

- to find out the proportion of tuberculosis patients infected with HIV

**2. Methods**

**2.1. Study design**

This is a cross-sectional study/survey to find out the proportion of tuberculosis patients infected with HIV in the region. As part of regional tuberculosis and HIV infection, the investigator will select nine sites from the region. Selection criteria of the sites are that they should have laboratory technician, well performing DOTS programme, laboratory reagents, functional x-ray machine, functional refrigerator to store blood sample and be accessible for supervision. All tuberculosis 15 years old or more patients on treatment will be included in the study.

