**1.4. Tuberculosis programme in southern region**

Southern Nations, Nationalities and peoples Regional State (SNNPRS) is one of the Federal

States of Ethiopia. The region has a population of about 14 million. Ninety-three percent of the population live in rural areas. The health service coverage and user rate is about 50 % and 32 %, respectively.

In 1995, DOTS started as a pilot project in three zones and four health institutions of the southern region of Ethiopia. Now, all hospitals and health centres provide DOTS to tuberculosis patients. As a result, number of tuberculosis cases has increased. However, the case detection rate was not in proportion to the programme coverage.[7]

Low coverage of the health service, low use rate and poverty compromised access to tuberculosis care. As a result, the case detection rate is below the global target. Thus, we need to find better ways of addressing the tuberculosis problem.[7]

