Other reasons for delay are the inability of health workers to detect tuberculosis patients in the clinic. Therefore, understanding the main presenting symptoms of tuberculosis by health workers is important to increase tuberculosis case detection. Some studies identified the main symptoms described by tuberculosis patients. Specifically cough, night sweats, weight loss and tiredness are among the symptoms with high predictive value.[23, 24] A study conducted in Ethiopia described the main symptoms of tuberculosis patients and found that about 95 % had cough as a presenting symptom after two weeks.[25]

Health workers should have high index of suspicion of tuberculosis to increase case detection. This demands simple symptom score to improve diagnosis. This may reduce the duration of health service delay. This has been a practice for childhood tuberculosis case finding though it was not conclusive to date.[26] A study carried out in Ethiopia used tuberculosis symptoms and x-ray results to identify its diagnostic value. They found sensitivity and specificity of above 90%. However, about 40 % patients were below the cut-off point.[27] In addition, the cost and low access of radiological services in the country remains a practical problem to tuberculosis patients. Therefore, simple and applicable tuberculosis scoring system would play an important role in case finding by health and community health workers.

In addition, the nature of mycobacterium gives an opportunity to improve case finding. Mycobacterium tuberculosis remains viable for longer period when stored at a room temperature. A Study from Malawi showed that it could stay viable for about four weeks.[28] The fact that the bacilli could stay viable for longer time under room temperature in a humid set up could be an opportunity to tuberculosis control programme. Therefore, community health workers could collect and transport sputum specimen over short period for laboratory examination for tuberculosis bacilli.

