**Study - V**

This is a cross-sectional study or survey to find the proportion of tuberculosis patients infected with human immunodeficiency virus. The investigator will select ten sites from the region as part of regional surveillance of HIV infection among tuberculosis patients. The study will include all tuberculosis patients diagnosed over six months period. Trained laboratory technicians and health workers from tuberculosis clinic /data collectors/ will administer pr-tested questionnaire and record socio-demographic variables as age, sex, residence, classification and category of tuberculosis. Tuberculosis patients will give serum for HIV testing. The laboratory technicians will label and store the blood specimen as per the recommendation for HIV testing. They will transport the specimen to regional reference laboratory under cold chain. Trained laboratory technologists in the regional reference laboratory will do HIV testing under national testing algorithm. The results will be anonymous and unlinked.

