**Serosurvey among tuberculosis patients in southern region**

Study site ______________ Date ___________

Patient code no _______________ Age __________ Sex __________

Address Urban ___________ Rural _______________

Diseases category a) New b) Relapse c) treatment after default

Disease classification a) smear positive b) smear Negative c) EPTB

Name of responsible health worker ________________

Signature ____________

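### Study V targets the HIV proportion among TB patients in the region, but discretionary site criteria exclude part of the region and nothing limits the conclusion to the kind of site selected

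*Protocol*

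**What the plan says.** Study Five, section 2.1, states the aim as "to find out the proportion of tuberculosis patients infected with HIV in the region". Sites are chosen by the investigator. No random or proportional selection is described. Besides a laboratory technician, a site must have "well performing DOTS programme, laboratory reagents, functional x-ray machine, functional refrigerator to store blood sample and be accessible for supervision". All TB patients aged 15 or more on treatment at those sites are included.

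The number of sites differs between sections: "the investigator will select nine sites from the region" in Study Five, section 2.1, and "The investigator will select ten sites from the region as part of regional surveillance of HIV infection among tuberculosis patients" in section 6.2 (Study - V). That needs reconciling but is a separate matter. Both sentences describe a choice by the investigator for a regional purpose.

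Study Five, section 2.4, sizes the survey at 984 for an expected proportion of about 20% and a margin of 2.5%. Section 6.7 names the software and describes no estimator for this study. The serosurvey form records urban or rural address and "Disease classification a) smear positive b) smear Negative c) EPTB".

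On the setting, section 1.4 says "Ninety-three percent of the population live in rural areas" and "The health service coverage and user rate is about 50 % and 32 %, respectively". It also says that every hospital and health centre now gives DOTS. Section 3 remarks that "the cost and low access of radiological services in the country remains a practical problem to tuberculosis patients".

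**The concern.** The target covers TB patients across the region, and DOTS is given at every hospital and health centre. The survey can draw only on facilities that meet all the listed criteria. Where x-ray access is low and most people live in rural areas, facilities with a working x-ray, good programme performance and easy access may differ from the rest in the patients they see. If HIV infection also differs between those groups of patients, the proportion found at the selected sites is not the regional one. Testing more patients at the same sites would not change that.

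The regional HIV figure is what Study V is meant to deliver. Followed as written, the plan would let a selected-site proportion be reported as the regional one, with a 2.5-point margin that suggests more certainty about the region than the design can give.

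**Working it through.** **1. The plan's own figure.** Inputs from Study Five, section 2.4: z = 1.96, p = 0.20, d = 0.025.

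n = z² × p × (1 − p) / d² = 1.96² × 0.20 × 0.80 / 0.025² = 983.45, rounded up to 984. The stated figure is reproduced. The formula assumes a simple random sample of the target population, so the 2.5 points describe random error only.

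**2. Which criteria matter.** Blood is drawn, refrigerated and sent by cold chain to the regional laboratory (Study Five, section 2.3). The technician, reagents and refrigerator follow from that. Good DOTS performance, x-ray and accessibility do not. The point concerns these three.

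**3. What cannot be computed.** The documents give no HIV proportion by residence, disease class or type of facility, and no residence mix of TB patients, either in the region or at eligible sites. The actual bias therefore cannot be derived.

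**4. Illustration with assumed inputs.** Let s be the urban share of the sample, u the urban share of the region's TB patients and g the urban minus rural HIV proportion. If residence were the only difference,

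bias = (s − u) × g.

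Take u = 0.07, which borrows the general population's urban share (100% − 93%) as an assumption. Values of s and g are also assumed. Bias in percentage points:

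| Gap g | s = 20% | s = 30% | s = 50% |
|---|---|---|---|
| 0 | 0 | 0 | 0 |
| 10 points | 0.13 × 10 = 1.3 | 0.23 × 10 = 2.3 | 0.43 × 10 = 4.3 |
| 15 points | 1.95 | 3.45 | 6.45 |
| 25 points | 3.25 | 5.75 | 10.75 |

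If the region's TB patients were 20% urban instead (u = 0.20), a 10-point gap would give 0, 1.0 and 3.0 points, and a 25-point gap 0, 2.5 and 7.5 points. The sign reverses if rural patients have the higher HIV proportion, or if the sample is less urban than the region.

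**5. When the bias equals the planned margin.** With u = 0.07, g = 2.5 / (s − 0.07): 2.5/0.13 = 19 points at s = 20%, 2.5/0.23 = 11 points at s = 30%, and 2.5/0.43 = 6 points at s = 50%.

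**6. Effect on interval coverage.** Take rural HIV at 15% and urban at 25% (assumed), u = 0.07 and n = 984. The regional value is 0.07 × 25 + 0.93 × 15 = 15.7%. The crude expectation is 17%, 18% and 20% for s = 20%, 30% and 50%. With SE = √[p(1 − p)/984], coverage of a nominal 95% interval is Φ(1.96 − bias/SE) − Φ(−1.96 − bias/SE), which gives about 81%, 53% and 8%.

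**7. Precision after standardising.** Same assumed values, weights 0.07 and 0.93, simple random sampling within strata. Variance = Σ w² × p(1 − p)/n.
- s = 50% (492 per stratum): 0.0049 × 0.1875/492 + 0.8649 × 0.1275/492 = 0.000226, so the half-width is 1.96 × 0.0150 = 2.9 points.
- s = 30% (about 295 urban, 689 rural): 0.000163, so the half-width is 1.96 × 0.0128 = 2.5 points, against 2.4 for the crude 18%.

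**The case against.** Much of the opposing case stands.

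- A reader might infer that the plan fixes an unweighted estimate. It does not. Section 2.4 of Study Five is a sample-size formula and section 6.7 names software. Weighting may be set out in an analysis plan that is not shown, and residence and disease class are collected, so nothing rules it out.
- A reader might infer that the estimate is biased upwards by more than 2.5 points. The documents do not support a direction or a size. The 93% rural figure describes the general population, not TB patients on treatment, and rural patients can attend eligible sites. With no HIV gap the bias is zero. With a 10-point gap, u = 0.07 and a sample 20–30% urban, it stays below the margin.
- A reader might infer that x-ray sites see more smear-negative disease, and that disease class is related to HIV. Neither is stated. The remark on radiology is a literature-review comment about the country, and section 6.1, which places TB diagnosis in health centres, says nothing about which facilities have x-ray.
- The objective in section 5.2 and in Study Five, section 1, carries no regional qualifier. The design section does, however, and section 6.2 and the form's title also place the survey at regional level.
- Reweighting the patients who were included cannot represent facilities that had no chance of selection.

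None of this removes the mismatch. The regional target and the site criteria are both fixed in the protocol, and no passage limits the conclusion to the kind of site chosen.

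**Conclusion.** The point holds as a mismatch between target and sampled facilities. The investigator's choice of sites by programme performance, x-ray and accessibility supports a statement about TB patients at such facilities. The protocol offers it as a statement about the region. The arithmetic behind 984 is right, but its margin does not cover this error.

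The size is not known. The illustrations run from 0 to about 11 points and rest on assumed HIV gaps, an assumed residence mix at the sites, and the population's 7% urban share standing in for that of TB patients. They show that the error could be negligible or could exceed the margin, and do not say which. Study V is a descriptive survey separate from the randomised comparison, so the consequence is confined to how its result is defined and reported. The improvement is cheap and worth making.

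**What to change.** In Study Five:

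1. Define the crude figure as the HIV proportion among TB patients aged 15 or more at facilities meeting the section 2.1 criteria, and word the conclusion to match.
2. Report HIV proportions by residence and by disease class from the serosurvey form. The result is entered on the data collection format under the study number (section 2.3), so this remains possible with anonymous testing.
3. Add, as the regional estimate, a proportion standardised to the region's notified TB patients by disease class, and by residence if those counts exist. The Reporting paragraph of Study Two does not list residence among the reported items, so availability needs checking first. If there are no such counts, show the residence-specific proportions beside the estimate standardised by disease class.
4. State that standardisation corrects only the recorded patient mix, not other differences at the excluded facilities.

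The cost is a short extra analysis, a request for regional notification counts, and an interval somewhat wider than 2.5 points (up to about 2.9 in the illustration). No change to sites, patient numbers or forms is needed.
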